### Analyses

The primary intention of our intervention is to continue supporting interactions between Coaches and their groups, and follow students longitudinally to see if the *Academy* makes a tangible difference in long-term career choices. The hypothesis is that experimental students will have a higher likelihood of pursuing an academic career after the PhD, and that the proportion of URM and non-URM students will be more equal than the past extremely low rate for URM students. These dynamics will be measured through annual interviews with students and quantitative responses on their perceptions of the achievability, desirability, and their commitment to an academic career throughout graduate school and subsequent career steps. These career steps, such as arranging post-doctoral positions that will likely lead to a successful academic career, will provide interim measures.

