### Data collection

Both experimental and control students participate in yearly telephone interviews. Interview question topics include experiences in graduate school, experiences with mentors and PIs, issues of work/life balance and identity, and future career plans. *Academy* experimental students also respond to specific questions regarding their Coaches and the intervention programming. In the past, these interviews took place just before the annual *Academy* meetings or during the summer for Controls. This timing of interviews prior to the individual Coaching group meetings will continue. A sample interview protocol is included in Additional file 4. Prior to their yearly interview, students will complete a pre-interview online survey in which they provide details about fellowships and grants, changes in skill sets, perceptions on the achievability and desirability of an academic career, and current commitment to an academic career. A sample pre-interview survey protocol for *Academy I* is included in Additional file 5. Both *Academy I* and *Academy II* students are asked to discuss their academic experiences over the past year, and to reflect on what will be important for them in the near future. However, *Academy I* students are asked questions related to their early experiences in graduate school, while *Academy II* students are asked questions related to their experiences finishing graduate school and moving on to the next stage of their careers. To compare professional accomplishments as objective measures of possible differences between *Academy* and control students, we intend to obtain a full curriculum vitae from each student about 6 months after graduation.

During *Academy* meetings, daily online surveys obtained evaluative and feedback information about the meeting activities as well as information on impact in real time. Additionally, a virtually complete audio record of all meeting activities was obtained. This included audio recordings throughout the Coaching Group meetings; each Coach was provided with a small digital recorder that was on during all of their discussion. Individual meetings between Coaches and students were NOT recorded, however, to provide a deeper level of privacy to promote open conversations even about delicate topics. *Academy* students also answer interview and survey questions specific to the *Academy* intervention including daily evaluations of the *Academy* meetings in 2011 (Academy I only), 2012, and 2013.

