Finally, each of the Coaching Groups was assigned one of our PhD level social scientist Research Associates who observed and took field notes during their meetings. Given that we only had 3 Research Associates and 10 or 6 Coaching Groups, they were unable to be with their groups continuously but rather periodically throughout the meetings.

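### Interviews that disclose the arm, and a postdoc measure that is a forecast, leave part of the career comparison open to assessor bias

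*Protocol article*

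**What the plan says.** The Analyses section states the hypothesis that "experimental students will have a higher likelihood of pursuing an academic career after the PhD". It is to be measured by annual interviews and by "quantitative responses on their perceptions of the achievability, desirability, and their commitment to an academic career". Career steps supply interim measures, with one example given: "These career steps, such as arranging post-doctoral positions that will likely lead to a successful academic career, will provide interim measures".

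Under Data collection, "Both experimental and control students participate in yearly telephone interviews", but the content differs by arm: "Academy* experimental students also respond to specific questions regarding their Coaches and the intervention programming". A full CV is to be obtained about 6 months after graduation. Its stated purpose is "To compare professional accomplishments as objective measures of possible differences between *Academy* and control students".

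The same section reports that "each of the Coaching Groups was assigned one of our PhD level social scientist Research Associates who observed and took field notes during their meetings". There were three such Associates, present periodically. The Study design section refers to a single team covering both research and programme design. The section on activities between meetings says that the new grant pays for that team to deliver further material and also for the comparison with controls. Qualitative methods and analysis has the interviews interpreted with the help of the researchers' own knowledge, including the four theories on which the Academy is built.

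**The concern.** Three features meet in the same comparison. One named measure depends on someone's view of where a position will lead. One data source shows the arm to whoever conducts the interview or reads it whole. The people who study the students also built the programme and sat in on one arm's groups; no matching contact with controls is described.

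In that setting, a doubtful postdoc or an ambivalent career plan can be read more generously for a student whose coaching the reader watched. The likelier direction is towards the hypothesis, although a stricter reading is also possible. Once outcomes have been coded with the arm known, the coding cannot be unmasked afterwards without doing it again.

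**Working it through.** **What the text supports, source by source**

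| Outcome source | Needs an assessor's judgement? | Is the arm visible? |
|---|---|---|
| Annual interview | Yes, if coded for an arm comparison | Yes, by design, to the interviewer and to readers of the full transcript |
| Postdoc expected to lead to an academic career | Yes; no criterion in the article | Not stated |
| CV accomplishments | Partly; items such as papers, grants and positions are largely factual | Not stated; an Academy entry would reveal it |
| Self-rated achievability, desirability, commitment | No; the student completes the survey | Known to the student, so any bias is response bias |

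Assessor bias is therefore built into the conditions of the first source, a risk for the second and third, and not an issue for the fourth.

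**Size, for scale only.** The article gives no figure to reproduce: no outcome rate, effect size, alpha or power. Everything below except the arm sizes is an assumption.

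*Step 1: false difference from reading alone.* Let *a* be the share of students whose next step is ambiguous, and *g* the gap between arms in how often such a step is read as academic. With no true effect, the arms differ by *b* = *a* × *g*.

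- Central case: *a* = 0.30, read as academic in 60% (Academy) against 45% (control). *b* = 0.30 × (0.60 − 0.45) = 0.045, or 4.5 points.
- Low: 0.20 × 0.10 = 0.02, or 2 points.
- High: 0.40 × 0.20 = 0.08, or 8 points.

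*Step 2: what such a difference does at these sample sizes.* Arm sizes from Student recruitment: Academy I 100 vs 104, Academy II 60 vs 61, pooled 100 + 60 = 160 vs 104 + 61 = 165. For a two-sided 5% test of two proportions, the chance of a significant result favouring the Academy is approximately Φ[(*b* − 1.96·SE₀)/SE₁]. SE₀ uses the pooled proportion and SE₁ the separate proportions.

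Worked case: pooled cohorts, control rate 0.30, *b* = 0.05.

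- Pooled proportion = (160 × 0.35 + 165 × 0.30)/325 = 0.3246
- SE₀ = √[0.3246 × 0.6754 × (1/160 + 1/165)] = 0.05195
- SE₁ = √[0.35 × 0.65/160 + 0.30 × 0.70/165] = 0.05191
- (0.05 − 1.96 × 0.05195)/0.05191 = −0.998, and Φ(−0.998) = 0.159

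Over control rates of 20%, 30% and 50%, against a nominal 2.5% in that direction:

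| Assumed bias | Pooled | Academy I | Academy II |
|---|---|---|---|
| 3 points | 7.8–9.7% | 6.3–7.5% | 5.1–6.0% |
| 5 points | 14.5–18.9% | 10.6–13.5% | 7.9–9.6% |
| 10 points | 44.1–54.9% | 29.9–37.8% | 19.5–24.4% |

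The 10-point row lies above the 2 to 8 point range of Step 1 and is shown only to mark the trend. The calculation treats students as independent and the outcome as yes/no; the article specifies neither for this comparison.

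**The case against.** The strongest reply is that a reader might infer that all career outcomes are read with the arm known by the people who ran the Academy. The article does not say that. It does not name who interviews, who classifies postdocs or who reads CVs, and it describes neither masked nor unmasked coding. An article commonly leaves such procedures to the full protocol, so its silence is not evidence of unmasked reading. This part of the reply stands, and it limits what can be claimed about postdocs and CVs.

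Other parts stand as well. The postdoc wording is an example of an interim career step, not a scoring rule, and the hypothesis concerns the later career. The analyses of variance under Quantitative methods and analysis use surveys and meeting evaluations that students complete themselves. The grounded-theory work is described as theory-building; nothing says that it classes students as academic or not. Nor does anything say that Academy membership would be scored as a CV accomplishment. The interview protocol is in an additional file that is not shown, so how open the questions are cannot be judged.

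Two things remain. The Analyses section itself names interviews as a way of measuring the hypothesis, and Data collection makes those interviews disclose the arm. The only interim measure given as an example is worded as a prediction. Both are in the text and do not depend on silence.

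**Conclusion.** The concern holds in a limited form. Knowledge of the arm is explicit in the design for interviewers and for anyone who reads a full transcript. For the classification of postdocs and CVs it is a risk, raised by the overlap between research and programme roles and by a measure stated as a forecast. It does not touch the self-rated survey items.

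The size is unknown. The range of 2 to 8 points rests wholly on assumed shares of ambiguous cases and assumed reading gaps. It shows only that a modest gap would matter at these sample sizes: with both cohorts pooled, 5 points would raise the chance of a false positive in favour of the Academy from 2.5% to about 14–19%.

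This is a worthwhile improvement to make now, not a defect that invalidates the trial. The analyses and the CV collection are described as still to come, and the Discussion expects at least three more years of follow-up.

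**What to change.** Before any outcomes are read:

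1. Replace the forecast wording with a rule on observed features, such as position type, employer type and stated faculty goal, and apply it identically in both arms. This does most of the work, because it leaves less to judge.
2. For arm comparisons drawn from interviews, code only the questions asked of both arms, from transcripts with the Academy block and all references to arm, Academy or Coach removed.
3. Let no Research Associate code students from a Coaching Group he or she observed. With three Associates and one assigned to each group, two remain available for every Academy student.
4. Remove Academy entries from CVs before accomplishments are counted.

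The cost is some redaction time from existing staff; no new data are needed. Masking will be incomplete. A student's own account may reveal the arm, and redaction cannot change how an interviewer who knew the arm put the shared questions. About half of each meeting was full-group time, so Associates may also recognise students from other groups. The unmasked grounded-theory work on how coaching functions can continue separately.

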### Data collection

Both experimental and control students participate in yearly telephone interviews. Interview question topics include experiences in graduate school, experiences with mentors and PIs, issues of work/life balance and identity, and future career plans. *Academy* experimental students also respond to specific questions regarding their Coaches and the intervention programming. In the past, these interviews took place just before the annual *Academy* meetings or during the summer for Controls. This timing of interviews prior to the individual Coaching group meetings will continue. A sample interview protocol is included in Additional file 4. Prior to their yearly interview, students will complete a pre-interview online survey in which they provide details about fellowships and grants, changes in skill sets, perceptions on the achievability and desirability of an academic career, and current commitment to an academic career. A sample pre-interview survey protocol for *Academy I* is included in Additional file 5. Both *Academy I* and *Academy II* students are asked to discuss their academic experiences over the past year, and to reflect on what will be important for them in the near future. However, *Academy I* students are asked questions related to their early experiences in graduate school, while *Academy II* students are asked questions related to their experiences finishing graduate school and moving on to the next stage of their careers. To compare professional accomplishments as objective measures of possible differences between *Academy* and control students, we intend to obtain a full curriculum vitae from each student about 6 months after graduation.

During *Academy* meetings, daily online surveys obtained evaluative and feedback information about the meeting activities as well as information on impact in real time. Additionally, a virtually complete audio record of all meeting activities was obtained. This included audio recordings throughout the Coaching Group meetings; each Coach was provided with a small digital recorder that was on during all of their discussion. Individual meetings between Coaches and students were NOT recorded, however, to provide a deeper level of privacy to promote open conversations even about delicate topics. *Academy* students also answer interview and survey questions specific to the *Academy* intervention including daily evaluations of the *Academy* meetings in 2011 (Academy I only), 2012, and 2013.

Finally, each of the Coaching Groups was assigned one of our PhD level social scientist Research Associates who observed and took field notes during their meetings. Given that we only had 3 Research Associates and 10 or 6 Coaching Groups, they were unable to be with their groups continuously but rather periodically throughout the meetings.

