A number of programs have focused on improving the quality of mentoring through systematic mentor training [9-12]. Although the findings of these training programs are encouraging, we argue that mentoring as a *construct* is limited for four main reasons. First, mentors face many competing, sometimes incompatible, demands to both produce research for grant renewals and to enable students and postdocs to practice developing novel ideas. Second, good mentoring requires dedicated time, but time has become less available as PIs have to write more grants, lead research teams of increasing size and complexity, and focus on their own survival to support their research groups. Third, PIs constantly face the challenge of assessing the capabilities of different members of their lab group and making judgments of whom to promote to subsequent career stages. These assessments are often subject to unconscious or conscious biases about individual capabilities based on prior educational path and social assumptions based on gender, race, and ethnicity. Fourth, in the informal teaching and learning environment of research groups, a new member who comes from a background that is different from most group members will have a more difficult time figuring out how to excel within the group. As discussed later, we argue that a coaching model can serve to substantially offset these limitations of the traditional mentoring model.

A rare opportunity arose to develop and test our coaching intervention through the American Recovery and Reinvestment Act (ARRA) of 2009. Through an NIH Director’s ARRA Funded Pathfinder Award to Promote Diversity in the Scientific Workforce, we created, “*The Academy for Future Science Faculty*” (referred to henceforth as the *Academy*). The *Academy* recruited established senior life scientists with demonstrated expertise in mentoring young scientists, and provided them with additional training to serve as Coaches in the *Academy*. We recruited two cohorts of PhD students: one just before they started the PhD (*Academy I*) and one near the end of the PhD (*Academy II*). These students were provided with an extensive and unique in-person and virtual coached experience over 2–3 years.

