### Student recruitment

On April 10, 2011, an email describing the *Academy* was sent to biomedical graduate school leaders who were members of the GREAT group, graduate directors at other non-medical major research training universities, and leaders of undergraduate diversity STEM programs throughout the U.S. This date was chosen because it was just before the April 15 common deadline for students to make the final decision of where to pursue their PhDs among the offers of acceptance they had received. Those receiving the emails were asked to forward it to incoming PhD students, or undergraduates they had advised who were starting the PhD in fall 2011. It was advertised as multi-year professional development program particularly designed for those with a strong interest in a future academic career. It was made clear from the start that it was a randomized controlled trial of the program; applicants would not be reviewed, ranked or chosen based on credentials or prior experience. Three hundred and fifty students applied for the *Academy*, representing a wide variety of PhD programs in the U.S. From this applicant pool, 100 students were selected to participate in the *Academy*, and 104 students were selected as study controls who received no intervention. The 204 total students recruited for *Academy I* represents the maximum number of students that could be supported under our funding. Eligibility to participate in the *Academy* required: 1) an expressed interest in an academic career in science; 2) U.S. citizenship or permanent residency; and 3) first year PhD student status.

In April, 2012, a similar email was sent to the leaders of biomedical PhD training programs describing the second round of the *Academy II*, but this time asking them to forward it to all PhD students who were within 12–18 months of completing their degrees. Approximately 340 applications were received and were stratified and randomized. For this study, 60 were chosen for *Academy II*, and 61 were chosen for controls (to account for anticipated dropouts of the study) (Figure 1). As we anticipated more drop-offs from beginning PhD students compared to those finishing the PhD, the *Academy II* group is smaller than the *Academy I* group.

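### For Academy II, a full CV taken after graduation mixes accomplishments from before and after randomisation; comparing the arms on it unadjusted would cost precision, though it would not cause bias

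*Protocol article*

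**What the plan says.** Under Student recruitment, leaders of PhD programmes were asked in April 2012 to "forward it to all PhD students who were within 12–18 months of completing their degrees". From the applications, "60 were chosen for *Academy II*, and 61 were chosen for controls".

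Under Data collection, the article gives the purpose of the CV as "To compare professional accomplishments as objective measures of possible differences between *Academy* and control students", and continues: "we intend to obtain a full curriculum vitae from each student about 6 months after graduation". The sentence covers both cohorts. It mentions no CV at entry, no restriction to items dated after randomisation and no adjustment for earlier items. Quantitative methods and analysis announces analyses of variance between groups such as experimental and control, and names no covariate.

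The main hypothesis, under Analyses, is a different outcome: that "experimental students will have a higher likelihood of pursuing an academic career after the PhD". Interim measures are career steps, such as "arranging post-doctoral positions that will likely lead to a successful academic career, will provide interim measures".

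**The concern.** A CV is cumulative. For a student randomised late in the PhD, it lists the publications, fellowships and awards of the earlier PhD years next to those of the last year or two. Only the later items can carry an effect of the Academy. The earlier ones add variance to the comparison and nothing to the difference between arms.

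The issue comes from combining two choices the article does state: a late entry window and a full CV taken once, after graduation. It is much smaller in Academy I, which enters just before the PhD starts, so that the whole PhD follows randomisation.

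At stake is the precision of the comparison that the article itself calls objective, in the smaller of its two cohorts. A real effect on output could be missed. Differences in earlier records that arose by chance would also sit unseen inside the estimate.

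**Working it through.** The article gives no power calculation, effect size or standard deviation for the CV comparison, so there is no figure of its own to reproduce.

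**Inputs from the article**
- Entry to graduation in Academy II: 12–18 months, as expected at invitation.
- Graduation to CV: about 6 months.
- Arms: 60 and 61.

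**Assumptions, not in the article**
- PhD length of 5–6 years.
- Poisson counts of items.
- Output per month either constant, or three times higher after entry.

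**Step 1: time on the CV.** Post-entry time is 12 + 6 = 18 to 18 + 6 = 24 months. The share of time before entry is f = 1 − post-entry months / (PhD months + 6).

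| PhD | Entry before finish | Post-entry / total months | Share before entry |
|---|---|---|---|
| 5 years | 18 months | 24 / 66 | 64% |
| 5 years | 12 months | 18 / 66 | 73% |
| 6 years | 18 months | 24 / 78 | 69% |
| 6 years | 12 months | 18 / 78 | 77% |

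With a PhD of 4–7 years the range widens to 56% (1 − 24/54) through 80% (1 − 18/90). Anything on the CV from before the PhD would come on top.

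**Step 2: precision at a constant rate.** The absolute effect is the same whether whole-CV or post-entry items are counted. The variance of a Poisson count is proportional to the number of items, so the variance ratio is 1/(1 − f).
- Lowest: 66/24 = 2.75, standard error ratio √2.75 = 1.66.
- Highest: 78/18 = 4.33, standard error ratio √4.33 = 2.08.

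**Step 3: precision if output triples after entry.** Each post-entry month now counts three times.
- 5-year PhD, 18 months: 42 / (42 + 3 × 24) = 42/114 = 37% of items predate entry. Variance ratio 114/72 = 1.58, standard error ratio 1.26.
- 6-year PhD, 12 months: 60 / (60 + 3 × 18) = 60/114 = 53% predate entry. Variance ratio 114/54 = 2.11, standard error ratio 1.45.

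**Step 4: what this means with 60 and 61 students.** Take, for illustration only, a standardised effect of 0.5 on the post-entry count and a two-sided 5% test. Power is Φ(0.5 × √(60 × 61/121) / R − 1.96), where R is the standard error ratio and √(60 × 61/121) = 5.50.
- Post-entry items only, R = 1: Φ(2.75 − 1.96) = 0.79.
- Whole CV, constant rate: Φ(2.75/1.66 − 1.96) = 0.38 down to Φ(2.75/2.08 − 1.96) = 0.26.
- Whole CV, tripled rate: Φ(2.75/1.26 − 1.96) = 0.59 down to Φ(2.75/1.45 − 1.96) = 0.47.

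**Step 5: share of items, not of time.** Earlier items are the majority only if the post-entry rate is less than (pre-entry months / post-entry months) times the earlier rate. That limit is 42/24 = 1.75 in the first case of step 3 and 60/18 = 3.33 in the second. The article gives no rate of output, so the majority by count cannot be settled from it.

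**The case against.** The strongest reply is that the article describes what is collected, not what is counted. It never says that whole-CV totals are the endpoint. CV entries usually carry dates, so a full CV is exactly what makes a post-randomisation count possible, and the rule may stand in an analysis plan that is not shown. This stands in part: the article cannot be charged with an error, and all the sizes above are conditional on comparing the CVs as they stand. It does not dispose of the point. The article fixes the measure, its timing and its use between arms, and for Academy II a more precise comparison is available from the same document.

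Four stronger readings are tempting, and the article does not support them.
- A reader might infer that most accomplishments compared predate randomisation. That is so for elapsed time under the assumed PhD length. By count it fails if output is concentrated late (step 5).
- A reader might infer bias. Applicants were stratified and randomised, so earlier records are balanced in expectation. A chance imbalance is part of ordinary sampling error, and the loss is one of precision.
- A reader might infer that the main result is at risk. The hypothesis concerns pursuit of an academic career after the PhD, and the CV is a supporting measure.
- A reader might want postdoctoral positions already arranged at entry to be excluded. That needs a baseline item for Academy II which the article does not describe, and the article does not tie those positions to the CV.

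The contrast with Academy I is also one of degree, since a full CV there lists work from before the PhD too.

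**Conclusion.** The point holds as a worthwhile improvement, limited to the CV comparison in Academy II. If the arms are compared on the CV with no separation of earlier items and no adjustment for them, the estimate is unbiased but less precise than it need be. The standard error of a count is about 1.7–2.1 times larger at a constant output rate, and about 1.3–1.45 times larger if output triples after entry.

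These figures rest on an assumed PhD of 5–6 years, Poisson counts, and the invitation window as a stand-in for the time from randomisation to graduation. Lasting differences in productivity between students, which Poisson counts leave out, would widen the gap. Output more than three times higher after entry would narrow it.

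**What to change.** State that the between-arm CV comparison uses items dated after randomisation, with the number of items dated before randomisation on the same CV as a covariate. Keep whole-CV totals as a description. The covariate takes up lasting differences between students and any chance imbalance in their earlier records. With it in a linear model, the estimated arm difference is the same whether the outcome is the post-randomisation count or the whole-CV count, so restriction and adjustment do not compete.

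The cost is one sentence in the plan and the coding of item dates, preferably by someone who does not know the arm. No new document has to be collected. There are two limits. Some items will have unclear dates, so a rule for them should be set before coding. Papers that appear soon after entry will still partly reflect earlier work, so dating reduces the dilution without removing it.
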